## Abstract

**Background:**

Chronic obstructive pulmonary disease (COPD) is the third cause of death worldwide. COPD is characterised by dyspnoea, limited exercise tolerance, and muscle dysfunction. Muscle dysfunction has been linked to dysregulation between muscle protein synthesis, myogenesis and degradation mechanisms. Conventional concentric cycling has been shown to improve several clinical outcomes and reduce muscle wasting in COPD patients. Eccentric cycling is a less explored exercise modality that allows higher training workloads imposing lower cardio-metabolic demand during exercise, which has shown to induce greater muscle mass and strength gains after training. Interestingly, the combination of eccentric and concentric cycling training has scarcely been explored. The molecular adaptations of skeletal muscle after exercise interventions in COPD have shown equivocal results. The mechanisms of muscle wasting in COPD and whether it can be reversed by exercise training are unclear. Therefore, this study aims two-fold: (1) to compare the effects of 12 weeks of eccentric (ECC), concentric (CONC), and combined eccentric/concentric (ECC/CONC) cycling training on muscle mass and function, cardiometabolic health, physical activity levels and quality of life in severe COPD patients; and (2) to examine the molecular adaptations regulating muscle growth after training, and whether they occur similarly in specific muscle fibres (i.e., I, IIa and IIx).

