## Methods

### Aim

The aim of this project is two folds. To investigate the effects of eccentric and concentric, eccentric, and concentric cycling training on (1) muscle mass, muscle function, functional performance, blood markers of cardiometabolic health, physical activity levels and quality of life in patients with severe COPD; and (2) the regulatory pathways for muscle synthesis (Akt/mTOR/p70s6K/rS6), MFR expression, muscle degradation (UP and autophagy), and miRs expression in the whole muscle and a fibre-type specific manner after training.

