### Experimental approach

We will compare the effects of CONC, ECC and the combination of CONC + ECC training on the changes in exercise performance (aerobic capacity and muscle strength), muscle mass, functional performance, levels of physical activity, quality of life, changes in biomarkers of cardiometabolic health (insulin resistance and lipid profile) and systemic inflammation. The proposed study is a multicentre randomised trial that will employ a 3 (groups) × 2 (measure times: Pre- and Post-) repeated measures design. The total duration of the proposed study is 14 weeks, including a 12-week training period and a testing week before and after the intervention. A stratified randomised assignment upon sequential number (by block) process will ensure that the experimental groups are balanced for FEV_1_, sex, and age. The allocation sequence will be performed by the multicentre coordinator. The training sessions will be conducted at three clinical centres in Santiago, Chile (Instituto Nacional del Torax, Hospital Clinico Universidad de Chile, Hospital Clinico Universidad Catolica). Assessors of all outcomes will be blinded to the group allocation of participants, which will not be revealed during the participation of the study.

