### Single muscle fibre isolation

Muscle samples will be freeze-dried in a tissue lyophiliser for 48 h. Next, a small segment (~ 3 µm) will be dissected under a light microscope using forceps and collected into a 10 µl loading buffer (1 × Lammelli’s buffer containing 10% β-mercaptoethanol), and stored overnight at − 80 °C. 30–60 single fibre segments will be collected from each sample as optimised previously [83]. Muscle fibre typing will be assessed by dot blotting. For each subject sample, a minimum of 9 muscle fibre segments will be pooled before electrophoresis.

Whole homogenate muscle specimen and isolated fibre type pools (type I, IIa and IIx) for the canonic protein synthesis Akt/mTOR/S6K1/rpS6 pathway, myogenic regulatory factors (Myogenin, MyoD, myf5, MRF4, and myostatin) and degradation (autophagy; LC3, p62, Parkin, beclin and ubiquitin–proteasome system; MuRF-1, atrogin-1, Need-1/4) systems will be analysed. Furthermore, NF-kB and MAPK pathways will also be explored for a relationship between inflammation and degradation systems. The protein content will be evaluated by Western blotting, and mRNA expression will be assessed by real-time qPCR before and after training.

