### Statistical analysis

The primary analysis will follow an intent-to-treat approach. A two-way analysis of variance (ANOVA) will be used to compare the three intervention groups and time (Pre- and Post-). If an interaction effect is found, a Tuckey´s post hoc test will be used for pairwise comparisons. Differences will be considered statistically significant at the 0.05 level (two-sided).

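### The stated group-by-time ANOVA has no fibre-type factor and so cannot test whether fibre types adapt alike; and with no primary outcome named, one 0.05 threshold covers all clinical outcomes

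*Protocol article*

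**What the plan says.** The analysis text is the short Statistical analysis section of the protocol article, and it serves both studies. The model is: "A two-way analysis of variance (ANOVA) will be used to compare the three intervention groups and time (Pre- and Post"-). This matches the Experimental approach section, which describes a "3 (groups) × 2 (measure times: Pre- and Post-) repeated measures design". If the interaction is significant, Tukey's "post hoc test will be used for pairwise comparisons". The threshold is general: "Differences will be considered statistically significant at the 0.05 level (two-sided"). The word primary appears there once, "The primary analysis will follow an intent-to-treat approach", and concerns who is analysed, not which outcome leads.

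The second aim in the abstract is to examine the molecular adaptations and "whether they occur similarly in specific muscle fibres (i.e., I, IIa and IIx"). The Aim section words it less sharply, as pathways and "miRs expression in the whole muscle and a fibre-type specific manner after training". The Experimental design section promises to examine how the response to training differs in whole muscle and in isolated fibres. The Single muscle fibre isolation section measures protein markers in whole homogenate and in "isolated fibre type pools (type I, IIa and IIx").

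The Participants section sizes Study 1 at 17 per group (22 recruited) from effect sizes of 0.6 to 1.2, citing muscle CSA and 6MWT together. The Molecular analyses section sizes Study 2 at eight per group (ten recruited) from effect sizes of 1 to 2.5.

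**The concern.** There are two separate problems, and the first is the stronger.

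**Aim against model.** Whether adaptations are similar across fibre types is a question about fibre type by time, and by group. A model with only group and time can be run once per pool, but it then gives one p-value per pool and no test of the difference between pools. A claim of fibre specificity would have to rest on one pool crossing 0.05 and another not. Fibre specificity is the rationale for the isolation work, so a central mechanistic conclusion is at stake.

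**No leading outcome.** The Discussion part of the abstract hopes to show that combined training gives the largest clinical gains, and the main Discussion expects the results to inform national guidelines. With no ranked outcome and one threshold, that conclusion can rest on whichever measure crosses 0.05. Tukey's test controls the three group pairs within one outcome and nothing across outcomes.

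**Working it through.** **1. The plan's own figures.** The test behind 17 per group is not stated. For a two-sided two-sample t-test at 0.05 with 80% power, the exact n per group is 45 at d = 0.6, 17 at d = 1.0 and 12 at d = 1.2. So 17 fits d of about 1.0, inside the stated range; other readings also give about 17 (paired d of about 0.72, or a three-group F test with f = 0.45). The sizing therefore does not show which outcome leads. For Study 2, eight per group fits d of about 1.5. At d = 1, the lower end of its stated range, power with eight per group is 0.46.

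**2. Fibre-type comparison through separate ANOVAs.** Suppose three pools share the same true effect and each separate test has power p. If the tests are independent, the chance that they do not all agree on significance is 1 − p³ − (1 − p)³.

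- p = 0.80: 1 − 0.512 − 0.008 = 0.48
- p = 0.46: 1 − 0.097 − 0.157 = 0.75

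The pools come from the same patients, so their tests are probably positively correlated, which lowers these figures; the documents give no correlation. With two pools only (type I and type II), the same formula gives 1 − 0.64 − 0.04 = 0.32 and 1 − 0.21 − 0.29 = 0.50.

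**3. Clinical outcomes at one threshold.** A sparing count from the outcome sections is 18: ten blood markers (glucose, insulin, four lipids, C-reactive protein, three cytokines), TUG, 6MWT, SGRQ-C total, CSA, MVC, VO2peak, POmax and one accelerometer measure. If all nulls are true and tests are independent, P(at least one) = 1 − 0.95^18 = 0.60. Simulating 2-df group-by-time tests (large-sample chi-square) with an assumed equal correlation between outcomes gives:

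| Outcomes | Correlation 0 | 0.3 | 0.5 | 0.7 |
|---|---|---|---|---|
| 18 | 0.60 | 0.51 | 0.41 | 0.29 |
| 24 | 0.71 | 0.61 | 0.47 | 0.32 |

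The row for 24 counts three SGRQ-C subscales, three CSA levels and three accelerometer measures instead of one each. The expected number of false interactions among 18 is 18 × 0.05 = 0.9 at any correlation.

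**4. After the change.** One primary outcome at 0.05 keeps the confirmatory error rate at 0.05. Splitting alpha over CSA and 6MWT at 0.025 each gives 1 − 0.975² = 0.049 if independent and at most 0.05 otherwise, but at d = 1.0 needs 21 instead of 17 evaluable patients per group.

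**The case against.** The strongest reply is that this is a condensed article. Its few sentences set a conventional significance level without ruling out further control, and rules for secondary and molecular markers normally sit in a full protocol or analysis plan that is not shown. That stands for exploratory markers: the absence of a multiplicity rule for them is not a finding here. It does not answer the mismatch between a stated aim and a stated model, or the sizing on two outcomes with neither named as leading.

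Two stronger readings are tempting, and the documents do not support them.

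- *False positives are near certain.* This needs roughly 100 near-independent tests with every null true (0.995 for 102). At an assumed correlation of 0.7 the same 102 tests give 0.51. Any such count also rests on assumptions: that every protein is assayed in all four preparations, and that miR-133 and miR-133a, and miR-181 and miR-181a, are distinct assays. Independence is implausible for measures such as total and LDL cholesterol, or VO2peak and POmax from one test.
- *The fibre-type aim is wholly untested.* The Aim section's wording can be met by running the group-by-time ANOVA within each pool. Only the abstract's question of similarity, and the promised look at differential response, need a comparison between pools. Nor does the article say that p-values will be compared across pools; that is the route left open if the model stays as written.

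**Conclusion.** The point holds in two parts.

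First, the two-factor model cannot answer the abstract's question about similarity across fibre types. This follows from the text and needs no numerical assumption. The 48% and 75% show how misleading per-pool significance could be; they assume equal true effects and independent tests, and are upper values if the pools are positively correlated.

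Second, no primary outcome is identified and a single 0.05 level is stated for all differences. For about 18 clinical outcomes the chance of at least one false interaction is roughly 0.3 to 0.6 under no effect. The count and the correlations (0 to 0.7) are assumptions. That is substantial inflation, not near certainty, and comparisons between groups within any one outcome are controlled by Tukey's test.

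**What to change.** **Study 2.** For each marker measured in the fibre pools, fit one mixed model with patient as a random effect, group between patients, and time and fibre type (I, IIa, IIx) within patients. Test fibre type × time to answer the abstract's question, and fibre type × time × group for differences by training mode. Call the three-way term exploratory: it was not part of the sizing, eight evaluable patients per group are planned, and the documents give no variance or within-patient correlation to size it. False-discovery-rate control across markers is one suitable option.

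**Study 1.** Before unblinding, name one of the two sizing outcomes as primary at two-sided 0.05. Quadriceps CSA is one choice, with the sponsor fixing the thigh level or average. Make the other a key secondary, tested only if the primary succeeds, and report the remaining outcomes as estimates with confidence intervals. Check the choice against the trial registration, which is not at hand here, and check that 17 evaluable per group fits the effect size expected for that outcome.

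**Cost.** The analysis wording changes and the data already planned suffice to fit the models. The small downside is fewer nominally significant findings. If the sizing check points to an effect well below d = 1.0, the plan should say that power is lower than stated.

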## Discussion

This project attempts to elucidate the effects of exercise training on muscle function and many clinical outcomes and a mechanistic approach to understand the muscle mass growth regulation in COPD patients. Although its methodology is straightforward, some debate existed regarding participant blinding and the need for a control group.

COPD is one of the most common chronic diseases worldwide, with an estimated 390 million people affected, with a global prevalence of 10.3% [85]. Although effective medications are available, COPD remains incurable and poorly controlled for numerous patients in many countries, rehabilitation has shown to improve quality of life and reduce mortality. Understanding muscle mass and function loss and recovery after exercise interventions is important to design the best clinical treatment. The effectiveness of clinical interventions in COPD is scarce. Thus, this study will compare three modalities of exercise training (eccentric, concentric and eccentric-concentric groups) in a clinical context in three hospitals in the region of Santiago, Chile. These hospitals will be implemented with the devices to perform eccentric cycling training within the public health system. This will help to support and update the Chilean COPD management guidelines.

### No control and no blinding

Due to ethical considerations, it was decided not to include a control group to provide an effective beneficial intervention (i.e., training) to all participants. We believe that comparing the three exercise interventions with a within- and between- group analysis approach will provide enough information to determine the effectiveness of these interventions for COPD patients on the included outcomes. Furthermore, as eccentric and concentric cycling exercises are different and depictable for patients and therapists, an intervention blinding is not possible with these kinds of interventions. However, assessors and biostatisticians will be blinded to the intervention, which should reduce detection and interpretation bias. The research group will be blinded when interpreting data and writing the conclusions.

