### Participants

Sixty-six participants diagnosed with severe COPD (FEV_1_ < 50% of predicted; quartiles 3 and 4 in the BODE [Body-mass index, airflow Obstruction, Dyspnoea, and Exercise] index) will be recruited via newspaper advertisements, posters, flyers, visits to local community centres and referral from associated centres. The sample size calculation revealed that based on an α level of 0.05 and a power (1-β) of 0.8, and effect sizes ranging from 0.6 to 1.2 found in similar outcomes (muscle CSA, 6MWT) in our preliminary data after eccentric training, and few studies using combined eccentric and concentric cycling [67–69], a minimum of 17 patients would be necessary per group for this study. However, 22 patients per group will be recruited to account for a typical dropout rate of 30% in long-term training studies. Accredited Ethics Committees from all three Hospitals and universities have approved this study. Any important modification will be informed to the ethics committees. All participants will obtain medical permission from a pulmonary medical specialist before taking part in the study. Exclusion criteria will be: current insulin therapy, long-term oxygen therapy, asthma, other concomitant pulmonary diseases, or other diseases that could affect physical activity [70, 71]. Participants will be instructed to continue with normal everyday activities yet be dis-encouraged from engaging in any unaccustomed training or supplementary nutrition and will be fully informed of the nature and possible risks of all of the experimental procedures before providing their written informed consent. Written informed consent will be obtained from the multicentre coordinator. Criteria for discontinuing intervention will be upon participant request or worsening disease. Patients will receive an initial report for all their clinical assessments, which will be upgraded at the end of the study participation. Participants will be coded as sequential number upon recruitment. A Data Monitoring Committee (DMC) will not be necessary as it will be a short intervention and with sample size that can be handle by the research team. Adverse events will be collected and reported appropriately. All personal information will be coded, and data collected will be kept confidential, and only the PI and multicentre coordinator of this study will have access to the files. The computer will be held in the PI office.

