### Implication for practice

Muscle cross-sectional area, muscle function, functional performance, aerobic capacity, daily physical activity, and quality of life will be assessed before and after training. Muscle biopsies of vastus lateralis will be performed before and after training in severe COPD patients, from which muscle protein synthesis and degradation pathways will be analysed in a fibre specific manner.

The results from this study will provide important knowledge regarding the treatment of patients with COPD who are unable or non-compliant with conventional offered COPD rehabilitation settings as concentric cycling (i.e., endurance training) is the most provided exercise intervention for these patients. The study will also contribute to the existing knowledge regarding molecular mechanisms involved in the regulation of muscle mass in these patients.

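### With three trained arms and no untrained arm, the within-group Pre-Post analysis cannot determine effectiveness; only between-arm differences in change can carry the conclusions

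*Protocol article*

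**What the plan says.** The section on control and blinding in the Discussion says that "it was decided not to include a control group to provide an effective beneficial intervention (i.e., training) to all participants". It goes on to express the belief that comparing the three programmes with a "within- and between- group analysis approach will provide enough information to determine the effectiveness of these interventions" on the included outcomes.

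Under Experimental approach, the design is a "3 (groups) × 2 (measure times: Pre- and Post-) repeated measures design". Training protocols describes an active programme for each arm: concentric (CONC), eccentric (ECC) and combined (ECC+CONC). No untrained arm, waiting list, run-in or external comparator is described.

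Statistical analysis specifies a two-way ANOVA with group and time, tested two-sided at 0.05. Tukey pairwise tests follow if an interaction is found. That section does not say how a time effect without an interaction is to be interpreted.

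Three other statements bear on the point:
- Participants are selected on FEV1 below 50% of predicted and on "quartiles 3 and 4 in the BODE" index (Participants). The index contains the 6-min walk distance (BODE index), and 6MWT is also a functional outcome (Functional performance).
- Patients and therapists cannot be blinded; assessors and biostatisticians are.
- Implication for practice says that "concentric cycling (i.e., endurance training) is the most provided exercise intervention for these patients".

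**The concern.** Without an untrained arm, the design identifies how the training modes differ from one another. It does not identify how much of the change in any one arm is due to training. The quoted sentence nevertheless names within-group analysis as part of what will establish effectiveness, and offers it in place of the control group.

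The practical risk lies in one plausible result: every arm improves, the time effect is significant and the interaction is not. As written, the sentence would allow that result to be reported as showing that all three programmes are effective. The Discussion says the work should help support and update national COPD guidance, so the wording of the conclusion matters.

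**Working it through.** **What each contrast estimates.** Let T be the training effect in an arm and C the change that would occur in any arm without a training effect.
- Within-arm Pre-Post change, or pooled time effect: T + C (for the time effect, T averaged over arms).
- Difference in change between arms 1 and 2: (T1 + C) − (T2 + C) = T1 − T2.

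C cancels only in the second line. With no untrained arm, nothing in the design estimates C alone.

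**Possible contents of C, from the document.**
- Repetition: 6MWT, timed up-and-go, knee-extensor MVC and incremental cycling are effort tests done at both times.
- Expectation: patients know their arm, and the respiratory questionnaire is self-reported. Blinded assessors do not remove this from a Pre-Post change.
- Regression to the mean: BODE-based selection includes the 6-min walk.
- Natural course: the Background gives a strength decline of about 4% per year in COPD, which pulls C the other way for strength.

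The document states no value for C, and no figure of the plan is in dispute here.

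**Illustration for 6MWT (assumed inputs).** Assume selection directly on 6MWT at 1 SD below the mean, the screening test also serving as the Pre value, no training effect (T = 0), and test-retest correlation r of 0.9 or 0.8.

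Regression to the mean = (1 − r) × 1 SD. SD of change = √(2(1 − r)). Standardised change c = the first divided by the second.
- r = 0.9: 0.10 / 0.447 = 0.22
- r = 0.8: 0.20 / 0.632 = 0.32

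Probability that a two-sided 5% paired t-test on the Pre-Post change is significant:

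| Patients analysed | r = 0.9 | r = 0.8 |
|---|---|---|
| One arm, 17 | 14% | 23% |
| All arms, 51 (3 × 17 planned minimum) | 35% | 60% |
| All arms, 66 (3 × 22 recruited) | 43% | 72% |
| Group × time interaction | 5% | 5% |

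If the shift is halved because selection is on FEV1 and a four-part composite, the pooled figures become 12% and 20% at 51 patients, and 15% and 24% at 66. All remain above the nominal 5%.

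**Other shared changes, same test, T = 0.** For c = 0.2, 0.3 and 0.5 SD of change, the pooled time effect at 51 patients is significant in 29%, 56% and 94% of trials. The interaction again stays at 5%. No passage supports a particular c; these figures show only how the test responds.

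**The case against.** The strongest reply is that the sentence speaks of comparing three interventions, that the stated aims are comparative throughout, and that it is an opinion in the Discussion and not an analysis rule. The operative analysis already makes the pairwise tests depend on an interaction, and those tests include every between-arm contrast of interest. The document also treats training as already shown to be beneficial, so the trial is not offered as proof that training beats no training.

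Much of this stands, and it confines the problem to interpretation. It does not dispose of it. The sentence expressly relies on within-group analysis, follows directly from the decision to have no control group, and is limited to relative effectiveness nowhere else in the article.

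The reply on size also stands in large part:
- Selection is on FEV1 and a composite, not on 6MWT alone, and the article does not say that the screening walk is the Pre value. The table is therefore an upper-end case for regression to the mean.
- MRI cross-sectional area, blood markers, accelerometry and biopsy measures are not effort tests and are not selected on.
- Timed up-and-go and MVC use the best of three attempts, which may reduce learning.

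A reader might infer that the trial needs an untrained arm. The document does not support that: the omission is disclosed and given an ethical reason, and the comparative question can be answered without one. A reader might also infer that the investigators will report all three programmes as effective, or that within-arm gains are bound to be inflated. Neither is stated. The first is only something the wording permits; the second fails because the shared change could be negative. Nor can the shift be expressed as a share of the planning effect of 0.6, because the article does not say on which SD that effect is scaled.

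**Conclusion.** The point holds as one of inference. The within-group part of the proposed analysis cannot determine effectiveness, because training effect and shared change are not separable in this design. The between-group part can support relative effectiveness.

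That conclusion rests on the design alone and needs none of the assumed inputs. The size does depend on them. In the upper-end 6MWT case, a time effect with no training effect behind it would be significant in about 35% to 60% of trials at 51 patients and 43% to 72% at 66, and roughly 12% to 24% if the shift is halved. The true size and direction cannot be read from the document and will differ by outcome. Sample size and choice of test are not affected. The change is worth making before results are known, because it governs what a time effect without interaction may be said to show.

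**What to change.** Reword the sentence in the section on control and blinding so that it claims comparative effectiveness only, and add to Statistical analysis:
- CONC is the active comparator, being the programme the article itself calls the most provided.
- Conclusions rest on the between-arm contrasts in change: ECC v CONC, ECC+CONC v CONC, and ECC+CONC v ECC.
- Within-arm Pre-Post changes are reported with confidence intervals as descriptive results.
- A time effect without an interaction shows neither effectiveness of the programmes nor their equivalence.

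The planned ANOVA and Tukey tests already supply these contrasts, so no patient, visit, procedure or arm is added. The cost is a few sentences and a narrower claim: the trial could say whether one mode is better than another, but not that each works.
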